### Epigenetic analyses

Emerging data support the concept that epigenetic mechanisms could drive the occurrence of allergic diseases. Epigenetic biomarkers have been pointed out, suggesting the role of selected methylation rate of the promoter region of Th1 and Th2 cytokine genes and of selected microRNAs expression. We will investigate these biomarkers with targeted DNA methylation analysis with the aim to link the MD adherence with the expression of these biomarkers and clinical outcome also through mediation analysis. Parallelly, we will attempt at epigenome-wide evaluation to explore the potential role of other epigenetic mechanism elicited by MD during pregnancy as protective action against allergy.

Cord blood will be collected by CT team in two EDTA-tubes (5 ml/each) and immediately transported to the laboratory for DNA and RNA extraction using the Extraction Kit (GE Healthcare, Chicago, IL, USA) performed by RT. One microgram of extracted DNA will be modified with sodium bisulfite to convert all unmethylated, but not methylated-cytosine to uracil. Bisulfite conversion will be carried out using the EZ DNA Methylation Gold Kit (ZYMO Research Co., Orange, CA, USA), according to the manufacturer’s instructions. The converted DNA will be stored at −80°C until used.

Targeted DNA methylation analysis of Th1 and Th2 cytokine genes will be performed by next-generation sequencing. Briefly, after the bisulfite treatment, a first step of PCR will be performed using primes generating amplicons of 300–400 bp. These primers will contain overhang adapters sequences at each 5’end (FW: 5′-TCGTCGGCAGCGTCAGATGTGTATAAGAGACAG-3′; RV: 5′-GTCTCGTGGGCTCGGAGATGTGTATAAGAGACAG-3′) that will be recognized in the second step of PCR. The first PCR conditions will be: one cycle at 95°C for 2 min followed by 32 cycles at 95°C for 30 s, [primer Tm] for 40 s, 72°C for 50 s, followed by a final extension step at 72°C for 6 min. To eliminate the excess of primers a first purification step will be performed by using AMPure magnetic Beads (Beckman-Coulter, Brea, CA, USA) with a ratio AMPure Beads/PCR products of 0.8. Then, a second step of PCR will be performed to add multiplexing indices and Illumina sequencing adapters. The condition of second PCR step will be: one cycle at 95°C for 2 min followed by eight cycles at 95°C 30 s, 55°C for 40 s, 72°C for 40 s, followed by a final extension step at 72°C for 5 min. Another purification with AMPure Beads was performed with a ratio Beads/PCR of 1.2. The quantification process and the check of amplicon quality will be performed respectively using Qubit^®^ 2.0 Fluorometer and Agilent 2100 Bioanalyzer DNA 1,000 Kit (Agilent Technologies, Santa Clara, CA, USA), according to the manufacturer’s instructions. The amplicon bisulfite library will be prepared. Phix control libraries (Illumina) [15% (v/v)] will be used to increase the diversity of base calling during sequencing. The sequencing will be performed with V2 reagents kits on Illumina MiSeq system (Illumina, San Diego, CA, USA). Paired-end sequencing was carried out in 251 cycles per read (251 × 2). Paired-end reads obtained from Illumina Miseq platform will be first assembled using PEAR tool with a minimum of 40 overlapping residues as threshold. The obtained sequences were analyzed using ampliMethProfiler pipeline software^1^ specifically designed for deep-targeted amplicon bisulfite sequencing (28). AmpliMethProfiler produces quality filtered FASTA files for each sample and directly extracts methylation average values and methylation profiles.

Global methylome analysis will be performed using Epigenome-Wide Association Study (EWAS) approach. Infinium TM Methylation EPIC Bead Chip by Illumina (San Diego, CA, USA) will be used to explore over 8,50,000 methylation sites per sample at single-nucleotide resolution, according to the manufacturer’s protocol.

For miRNA expression analysis, RNA will be extracted from the second EDTA tubes using Trizol protocol (Invitrogen, Life Technologies Europe BV, Monza, Italy) and TaqMan^®^ Array Human MicroRNA A Card v2.0, contains 384 TaqMan^®^ MicroRNA Assays, enabling accurate quantization of 377 human microRNAs (Applied Biosystem) will be used.

### Data entry

The CT will enter all collected data in a case report form using a single data-entry method. All data recorded in the case report form will be entered in the study database anonymously by the same researcher of CT staff. Study monitoring will be performed by an independent clinical trial monitor and will include on-site visits and telephone communications. The monitor will review the clinical forms for completeness, clarity and consistency and will instruct the RT personnel to make any corrections or additions. Then, the ST unaware of study cohorts will review the study dataset and will undergo data cleaning and verification according to standard procedures. Finally, ST will lock the database once it will be declared complete and accurate and the statistical analysis will be performed.

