### Study design

The PREMEDI Study will be a 9-month multi-center, randomized-controlled, parallel groups, prospective trial.

The study will involve three parallel teams: Research Team (RT), Clinical Team (CT), and Statistical Team (ST). The RT will be composed by physicians, molecular biologists, and dietitians. The CT will be composed by gynecologists, neonatologists, pediatricians, family pediatricians, allergologists, dietitians, and pediatric nurses. The ST will be composed by statisticians. A Study Monitor will overview the trial’s data management and analysis.

The RT will be dedicated to the enrollment and the randomization of participants. Then, the dietitians of the RT will perform the personalized nutritional counseling during the study phases. The CT will evaluate the participants and will collect data in anonymous form and will deliver data to the ST. The ST, unaware of study cohorts, will review the study dataset and will undergo data cleaning and verification according to standard procedures. Finally, ST will lock the database once it will be declared complete and accurate and will perform statistical analysis.

The graphical representation of study design is reported in Figure 1.

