### Allocation and blinding

The randomization and sequence allocation will be performed according to a computer-generated randomization list by building a stratified randomization with permutated block-randomization, stratified by maternal body mass index (BMI) (<25, 25–29.9, and ≥30 kg/m^2^), and parity (1 or >1), in an allocation ratio of 1:1 in blocks of 4–6. The Group #1 will receive standard obstetrical and gynecological follow-up and nutritional counseling to promote MD provided by certified dietitians, and the Group #2: will receive standard obstetrical and gynecological follow-up alone. Due to the nature of the RCT design, participants and RT will be aware of the group assignment. Whereas the allocation to Group #1 or Group #2 will remain unknown to the CT and ST.

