### Data and sample collection

At baseline, after the first evaluation by the RT and the collection of written informed consent form, the CT will collect the following variables in a dedicated chart: anamnestic and clinical features, personal and anthropometric data, socio-demographic factors, gestational age, allergies, number of cohabitants, pets, sports activities, use of drugs, smoking exposure, education level, family and living conditions. At enrollment a validated questionnaire on MD-adherence (Med Diet Score) and a 7-day food diary (five weekdays and two weekend days) will be collected. The 7-day food dairy data will be analyzed using specific software (Winfood–Medimatica Srl) by a dietitian. The intake of drugs, dietary supplements, pre-, pro-, and synbiotics will be recorded in the same chart. Then, the RT will schedule for each participant follow-up visits every 12 weeks from the enrollment (8–13 GW), then at 14–28 GW and at 29–40 GW. During these visits the CT will perform a full physical examination, anamnestic and clinical data collection, stool sampling (at least 3 g), 7-day food diary collection, Med Diet Score assessment. Each item assigns a score of 0 or 1, with a total score ranging from 0 to 14. The three categories of adherence to MD are divided in ≤5 (low), 6–9 (medium), ≥10 (high) score. Furthermore, to ensure and encourage the completion of the 7-day food diary, one week before each visit, the RT will remind the women by a phone call to fill in the food diary daily for the following week and to return them at the following visit. At delivery a cord blood sample (at least 10 ml) and a breast milk sample (collected within 24 h after delivery) (3 ml) will be collected. All neonatal clinical features will be evaluated by CT. After delivery, for all babies a follow-up visit will be planned every 3 months for the first 12 months of life and then every 6 months until the age of 2 years. At each visit the following procedures will be adopted by CT: full anamnestic and clinical evaluation, body growth assessment, occurrence of allergic disorders, occurrence of other conditions, 7-day food diary, child Mediterranean Diet Quality Index score (KIDMED) evaluation, stool sampling (at least 3 g). At each visit the persistence of breastfeeding will be also assessed and a breast milk sample will be eventually collected (3 ml). In addition, Skin Prick Testing using main pediatric allergens will be performed at 12 and 24 months. All collected data and documents will always remain confidential.

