### Statistical methods

All data will be collected in a dedicated database and analyzed by the ST. We will perform intention to treat (ITT) and per-protocol analysis. We will perform ITT analysis by considering the mother-child pair lost after randomization: (1) all missing values of the primary outcome will set to the worst outcome in both groups (equal-case scenario ITT) and (2) missing values of the primary outcome will set to the worst outcome in the Group 1 and to the best outcome in the Group 2 (worst-case scenario ITT). The worst outcome will be defined as the occurrence of ≥1 atopic condition at 24 months, in the offspring; the best outcome will be its opposite. The secondary outcomes will be evaluated using per-protocol analysis. The Kolmogorov-Smirnov test will be used to determine whether variables are normally distributed. Descriptive statistics will be used to summarize baseline characteristics. The Student *t*-test will be used to compare mean values of continuous variables for approximating a normal distribution. For non-normally distributed variables, the Mann-Whitney *U* test will be used. The χ^2^ test or Fisher exact test will be used, when appropriate. We will use a binomial regression model (BRM) to estimate the incidence of the main outcome, i.e., at least one atopic condition at 24 months, in the offspring. The response variable of the BRM will be the presence of at least one atopic condition at 24 months (0 = no; 1 = yes), and the predictor will be the treatment cohort (0 = Group 1; 1 = Group 2). To evaluate the effect of potential confounders on the main outcome, we will add each of them separately to the aforementioned BRM and we will evaluate the changes in the estimated risk ratios. The evaluated potential confounders will be sex (0 = female; 1 = male), age (months), cesarean delivery (0 = no; 1 = yes), born at term (0 = no; 1 = yes), breastfed for at least 2 months (0 = no; 1 = yes), weaning (months), siblings (number), exposed to passive smoking (0 = no; 1 = yes), mother smoked during pregnancy (0 = no; 1 = yes), and exposed to pets (0 = no; 1 = yes), drug use (0 = no; 1 = yes), antiseptics exposure (0 = no; 1 = yes), lifestyle (0 = rural; 1 = urban), dietary habits (0 = low MD-adherence; 1 = medium MD-adherence; 2 = high MD-adherence) and pollution exposure (0 = no; 1 = yes). BRM is among the most commonly suggested methods to report the results from randomized controlled trials with binary outcomes. Regression modeling allows adding baseline co-variables to increase the precision of the estimate and better control for potential confounders. Comparisons of taxa or gene abundance between groups will be carried out using pairwise Wilcoxon tests. Statistical significance of pangene prevalence will be verified through Fisher’s test with multiple-hypothesis testing corrections *via* the false discovery rate (FDR). Machine learning-based classification analysis will be done using the MetAML package (30) and by considering random forests (RFs) as back-end classifier for all the results. Results will be obtained through a fivefold cross-validation and averaged on 20 independent runs. To evaluate whether the significant associations for the cord blood analysis primarily reflect maternal adherence to MD, additional models adjusted for cord blood DNA methylation of the same CpG site and for miRNAs will be evaluated when examining the association between DNA methylation/miRNAs and childhood allergic sensitization. For DNA methylation, using a reference methylation Quantitative Trait Loci (QTL) library, we will evaluate the genetic control of methylation for the top 30 associated CpG sites identified from the mid-childhood meta-analysis for atopic sensitization, environmental and food allergen sensitization. We leveraged genetic-epigenetic information from the ARIES large-scale genome-mQTL analysis, which included 1,000 mother-child pairs^2^ (31). mQTL comparisons will be focused on the *cis* position (i.e., a genetic variant within ±500 Kb of a methylation locus) measured from cord blood, and with MAF ≥5%. The level of significance for all statistical tests will be two-sided, *p* < 0.05. An integrative approach that combines multi-omics data together with integrated clinical data analysis will be performed. Multivariable linear regression will be used to analyze associations differentially methylated regions in cord blood DNA with clinical measures of offspring. All significance values will be corrected to take into account the effect of multiple comparisons, using the Bonferroni adjustment. All analyses will be performed with Stata 16.1 (Stata Corporation, College Station, TX, USA), SAS^®^ version 9.4 (SAS Institute, Inc., Cary, NC, USA) and R version 3.4.1.

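### Monitor queries on the clinical forms go to the allocation-aware Research Team, so unblinded staff can alter the record of a clinically judged primary outcome

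*Protocol article*

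**What the plan says.** Under Allocation and blinding, "participants and RT will be aware of the group assignment". For the other two teams the same section promises the reverse: "the allocation to Group #1 or Group #2 will remain unknown to the CT and ST". Under Study design, "The RT will be dedicated to the enrollment and the randomization of participants", and Interventions has the RT dietitians give the Group 1 counseling.

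The outcome belongs to the CT. The section on the occurrence of allergic disorders has the CT examine the child and decide the diagnosis against standardized criteria. Data entry then states: "The CT will enter all collected data in a case report form using a single data-entry method". The forms are "entered in the study database anonymously by the same researcher of CT staff".

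The same section has the monitor check the clinical forms for completeness, clarity and consistency. The monitor then "will instruct the RT personnel to make any corrections or additions". Only after that does the ST receive the dataset for cleaning and lock.

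On diet data, Data and sample collection lists "7-day food diary collection, Med Diet Score assessment" among the CT's tasks at the pregnancy visits.

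**The concern.** Mothers cannot be blinded here, so blinded assessment and recording of the child's diagnosis are an important protection against differential misclassification. The outcome needs that protection because much of it is judgement. Eczema is diagnosed by counting clinical criteria. Urticaria episodes may be those seen by the parents. Asthma is described in terms of likelihood. The lower of the two food-allergy categories requires no positive test.

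The Data entry rule sends changes to those forms to the one staff team that knows the allocation and delivers the intervention, and that neither examined the child nor completed the form. The rule makes no exception for primary-outcome fields. If corrections or additions differed by arm, even without intent, the ST would receive an already altered dataset and could not detect this by being blind itself.

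**Working it through.** **1. Roles, set side by side**

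| Step | Team | Knows allocation? | Protocol section |
|---|---|---|---|
| Enrolls and randomizes | RT | Yes | Study design; Allocation and blinding |
| Counsels Group 1 | RT dietitians | Yes | Interventions |
| Examines child, decides diagnosis | CT | No | Evaluation of the occurrence of allergic disorders |
| Completes the form, enters the database | CT | No | Data entry |
| Corrects or adds to the form after monitor review | RT | Yes | Data entry |
| Cleans, locks, analyzes | ST | No | Study design; Data entry |

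The correction step is the only one between diagnosis and analysis that is assigned to an unblinded team. This is stated text, not something a condensed article has left out.

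**2. The plan's own sample size, to fix the number per arm**

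Inputs from Sample size calculation: 30% against 15%, two-sided alpha 0.05, power 0.80, drop-out 15%.

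- Unpooled normal formula: n = (1.960 + 0.842)² × (0.30 × 0.70 + 0.15 × 0.85) / 0.15² = 117.7.
- Inflated for drop-out: 117.7 / 0.85 = 138.5, which agrees with the stated 138 per group.
- Evaluable per arm after drop-out: 138 × 0.85 = 117.3, so 117 is used below.

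The sample size is not in dispute.

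**3. Hypothetical illustration**

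The documents give no rate of biased correction, so the rate m below is an assumption, shown over a range. Suppose the true incidence is 30% in both arms and a share m of Group 1 diagnoses is lost from the record. The recorded Group 1 incidence is then 0.30 × (1 − m), and Group 2 stays at 30%. For each pair of rates, the two binomial distributions (117 per arm) are enumerated exactly, and the probability is summed over all tables in which the two-sided 5% Pearson test rejects in favor of Group 1.

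| m | Recorded Group 1 incidence | Group 1 diagnoses lost (of 0.30 × 117 ≈ 35) | Chance of a false significant benefit |
|---|---|---|---|
| 0 | 30% | 0 | 2.5% |
| 2% (one in fifty) | 29.4% | about 0.7 | 3.2% |
| 10% (one in ten) | 27% | about 3.5 | 7.3% |
| 17% (one in six) | 25% | about 5.9 | 13.4% |

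The effect is negligible at the low end and roughly fivefold at the high end (13.4 / 2.5 ≈ 5.4). Nothing in the documents says where on this range the trial would fall.

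**The case against.** The strongest reply is that monitor queries concern completeness, clarity and consistency and do not re-decide diagnoses. The CT still makes every diagnosis against standardized criteria, skin prick tests are done at 12 and 24 months, and discordant diagnoses go to a further allergist unaware of the study aims. The word RT may even be a slip for CT. Most of this is fair and argues for a modest view of the likely bias. It does not remove the problem. Filling in or reconciling a missing or inconsistent eczema criterion can change whether a child counts as a case, the further allergist acts only on discordance, and a slip would still need correcting.

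A reader might infer three stronger things that the text does not support.

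- *That the rule breaks the blind.* RT corrections tell neither the CT nor the ST which arm a pair is in. The fault lies in who may alter the record.
- *That the CT is unblinded by handling diaries and the Med Diet Score.* Diet is a clue to allocation, not a disclosure of it: a control woman may score high and a counseled woman low. The CT is a mixed team, so whoever scores the mother need not diagnose the child. The article sets no separation within the CT, however, so a minor remark stands.
- *That the ST cannot be blind because* "the predictor will be the treatment cohort (0 = Group 1; 1 = Group 2"*.* A coding line in a protocol does not show that the analysts' dataset carries decoded arms, and the asymmetric worst-case scenario can be run after the primary model. No point is made of this.

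**Conclusion.** The point holds in a limited form. The Data entry rule gives allocation-aware staff, who deliver the intervention, authority to correct or add to forms that blinded staff completed, including the primary-outcome record, before the ST receives it. That is at odds with the protection set up under Allocation and blinding, and the two sections should be reconciled.

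The size of any resulting bias is unknown. The range of 3.2% to 13.4%, against 2.5% without bias, rests on assumed losses of 2% to 17% of Group 1 diagnoses, no true effect, 30% incidence and 117 evaluable per arm. It shows sensitivity and predicts nothing about this trial. The change is worth making because it is cheap and closes a route to bias that analysis could not repair afterwards.

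**What to change.** In Data entry, replace the RT as recipient of the monitor's instructions with the CT personnel who recorded the data. Add that each change is logged (old value, new value, who, when, why) and that the RT may not edit forms holding outcome data. The cost is a change of wording and a change log. No new visits, staff or sample size are needed.

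As a minor addition, state that the clinicians who diagnose the child are not shown the mother's food diaries or Med Diet Score. This asks only for a separation of forms within the CT. Passing the Med Diet Score to the RT, or making it self-completed, is not recommended: maternal adherence is itself a secondary outcome, and that would place it with the unblinded staff who gave the counseling.

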### Sample size calculation

Based on the results of the EUROPREVALL cohort (29), reporting a cumulative incidence for allergic diseases of 30%, and on the results of a previous pilot study performed at our center (unpublished data) showing a drop-out rate to this kind of intervention up to 15%, we estimated that 138 mother-child pair per group will be needed to detect a reduction in cumulative incidence of at least one allergic disease at 24 months from 30 to 15%, with a power of 0.80 at an alpha level of 0.05 (Pearson’s Chi-square, two-tailed test).

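### The 80% power stated for 138 pairs per group applies to observed outcomes, not to the two ITT analyses, which fill in lost pairs by rule

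*Protocol article*

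**What the plan says.** The Sample size calculation section of the protocol article takes a reduction in "at least one allergic disease at 24 months from 30 to 15"%, a "Chi-square, two-tailed test", and a pilot study "showing a drop-out rate to this kind of intervention up to 15"%. From these it reports that "we estimated that 138 mother-child pair per group will be needed", "with a power of 0.80 at an alpha level of 0.05". It states neither the variance formula nor how drop-out entered the figure.

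The Statistical methods section announces intention-to-treat and per-protocol analyses and calls neither of them primary. It gives two ITT rules for the primary outcome. In the first, "all missing values of the primary outcome will set to the worst outcome in both groups (equal-case scenario ITT"). In the second, called the worst-case scenario, a missing outcome counts as allergic disease in Group 1 (counselling) and as no allergic disease in Group 2 (standard follow-up). No ITT analysis of the outcomes as observed is described.

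**The concern.** The sample size rests on 30% against 15%. Those rates describe children whose outcome is known at 24 months; lost pairs enter only as a reduction in number. Under the ITT rules lost pairs stay in the denominator with an assigned outcome, so the two arms are no longer compared at 30% and 15%. Assigning an event to the same share of both arms pulls the rates together. Assigning events only to the counselling arm pushes them together faster and can reverse them.

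The stated power therefore belongs to one analysis, while the plan's ITT analyses are different ones. If the diet does halve allergic disease, a reader who attaches 0.80 to the ITT result expects a one-in-five chance of missing it. The real chance is larger, and a null ITT result would be read as stronger evidence against the diet than it is.

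**Working it through.** **Inputs.** From Sample size calculation: control rate 0.30, intervention rate 0.15, two-sided alpha 0.05, power 0.80, drop-out up to 0.15, N = 138 per group. From Allocation and blinding: 1:1 allocation. From Statistical methods: the two rules for missing outcomes. My assumptions: the same proportion d is missing in each arm, and missingness is unrelated to outcome.

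**1. Reproducing 138.** With unpooled variance, n = (1.96 + 0.8416)² × (0.30×0.70 + 0.15×0.85) / 0.15² = 117.7 per group. Allowing for 15% loss, 117.7 / 0.85 = 138.5, which agrees with the stated 138.

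**2. Power for observed outcomes.** After 15% loss, 138 × 0.85 = 117.3, so about 117 per group. The power of the Pearson test at 30% against 15% is 78.8% by the pooled formula,

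Φ{ [|p₁ − p₂|√n − 1.96√(2p̄(1 − p̄))] / √(p₁(1 − p₁) + p₂(1 − p₂)) },

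and 79.4% by exact binomial enumeration. With no loss (138 per group) it is 85%. The sample size is sound for this comparison.

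**3. Equal-case ITT.** Expected rates become 0.30(1 − d) + d in control and 0.15(1 − d) + d in intervention, with all 138 per group analysed. The difference shrinks to 0.15(1 − d), and the rates move towards 50%, where the variance is larger.

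| Missing | Control | Intervention | Power at 138 (formula) |
|---|---|---|---|
| 5% | 33.5% | 19.25% | 76.9% |
| 10% | 37.0% | 23.5% | 68.7% |
| 15% | 40.5% | 27.75% | 60.9% (exact 61.1%) |

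At 15% missing, the same formula solved for n gives about 216 per group for 80% power.

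**4. Worst-case ITT.** Control becomes 0.30(1 − d); intervention is again 0.15(1 − d) + d.

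| Missing | Control | Intervention | Chance of a significant benefit at 138 |
|---|---|---|---|
| 5% | 28.5% | 19.25% | 43.7% |
| 10% | 27.0% | 23.5% | 9.8% |
| 15% | 25.5% | 27.75% | 0.9% (exact) |

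The direction reverses once d > 0.15(1 − d), that is d > 0.15/1.15 = 13.0%. Beyond that point no sample size gives power to show benefit. At 15% missing, the exact chance of a significant result favouring control is 6.2%, so a non-significant result has probability 1 − 0.009 − 0.062 = 0.929, about 93%.

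**The case against.** **The sample size section makes no promise about ITT.** It ties 0.80 to a fall from 30% to 15% and does not mention imputation. That is right, and on observed outcomes the design delivers about 80%. But the only ITT analyses described for the primary outcome are the imputed ones, and nothing tells the reader which analysis the 0.80 belongs to.

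**A worst-case scenario is meant to be hostile to the intervention.** This also stands. Trials are not normally powered for such a bound, and 1% there is no sample-size failure in itself. It matters only because the plan lists the scenario as one of its two ITT analyses, without calling it a sensitivity analysis and without naming a primary one. The equal-case analysis, which treats both arms alike, also falls short.

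**Fifteen per cent is a ceiling.** True, and 61% is the figure at that ceiling. Equal-case power is still below 80% at 10% and at 5% missing.

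**The detail may sit in a separate analysis plan.** It may, but the point is not an omission. The article fixes both the sample size and the ITT rules, and the two do not fit together.

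**A tempting stronger reading: an arithmetic error.** Because 120 × 1.15 = 138, a reader might infer that drop-out was added by multiplying by 1.15 when dividing by 0.85 is correct. The document does not state the step, and the unpooled formula with the correct division gives 138.5. The route cannot be identified, and with 79.4% power on observed outcomes it hardly matters.

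**Conclusion.** The point holds as a mismatch between the sample size and the ITT rules. The figure of 138 per group supports about 80% power for comparing observed outcomes at 30% against 15%. It does not support 80% for either ITT analysis as written: equal-case power is about 61%, 69% and 77% with 15%, 10% and 5% missing, and the worst-case analysis has about a 1% chance of showing benefit at 15% missing. These figures assume equal loss in both arms, unrelated to outcome, and the plan's own rates.

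Two further inferences are not supported. The 138 is not shown to be miscalculated. Nor does the worst case at 15% missing mean that 99% of results would be non-significant: about 99% would show no significant benefit, but 6.2% would significantly favour control, which leaves about 93% non-significant.

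**What to change.** In Sample size calculation, state that the 0.80 power applies to the analysis of observed outcomes, and name that analysis so that it can be matched to one in Statistical methods. Beside it, give the equal-case power across 5–15% missing: about 77%, 69% and 61%, with the assumptions behind these figures. In Statistical methods, label the equal-case and worst-case analyses as sensitivity analyses, and describe the worst case as an unpowered bound whose expected direction can reverse at the planned drop-out ceiling.

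The 138 can stand, and no extra participants are needed. The cost is about a paragraph of text, and the power stated for the ITT analyses becomes less favourable than a reader would now assume.
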